**10.Statistical Analysis**

Baseline continuously distributed data will be presented as means and standard deviations unless the data is non-normal in which case the data median (25th/75th centiles) will be determined; categorical data by n (%). Given randomisation to treatment, baselines will not compared statistically (10-12). Intention to treat analysis will be undertaken. Within-group differences will be shown for each treatment group separately by a mean and a standard deviation (SD). Between-group comparisons will be performed using Student’s t testing if the data is normally distributed, and non-parametric testing if it is not. For all statistical analyses, a two-tailed P <0.05 will be considered to indicate statistical significance. Time to event analysis and logistic regression will be used to analyse outcomes. Statistical analysis will be performed using the STATA statistical computer package (StataCorp. 2013. Stata Statistical Software: Release 13. College Station, TX: StataCorp LP, USA).

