**Study Schedule**

**1: Patient characteristics**

- Patient confirmed to be SARS-CoV-2positive by PCR
- Patients able to give informed consent
- Patients who are hypoxic and requiring oxygen therapy
- Consent, inclusion and exclusion criteria. Patients will be assessed for the inclusion and exclusion criteria of the study by the consultant and consented by a doctor on the clinical team.
- Patient identifiers, admission date, age and sex
- Patient characteristics (yes/no): current smoking, diabetes, heart disease, chronic lung disease, chronic liver disease, chronic kidney disease, asthma, HIV, tuberculosis
- COVID-19 oxygen therapy being given, oxygen saturation on room air, oxygen flow.
- Anthropometric measurement –BMI, blood pressure, temperature, respiratory rate
- ECG
- Baseline bloods: Biochemical profile (BCP), full blood count (FBC), CRP, PCT, LDH, Troponin, Ferritin, D-Dimer, BNP, lactate
- Baseline ABG on room air, on enrolment
- Baseline PaO2 value
- Chest Xray prior to starting plasma transfusion
- ABO and RhD blood grouping and cross-matching
- Baseline SARS-CoV-2 Swab PCR with CT Value (indirect assessment of viral load) through Nasopharyngeal swab.
- Randomization into one of the 2 groups

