**3: Intermittent recording in case report form for 10 day or until discharge**

- Chest Xray 1 day after completion of plasma therapy or standard treatment and on Discharge
- ABG and PaO2 values after completion of plasma therapy or standard treatment on day 1,2,3 and then every 3 days and on discharge
- SARS-CoV-2 Swab PCR with CT Value , day 1 and 3 after plasma transfusion or standard treatment, every 7 days, and on discharge

*Criteria for discontinuation of the study*.

The study will be discontinued based on any adverse reactions such as transfusion reactions or may be withdrawn by the Ministry of Health decision on safety, or if any superior drug/intervention has been identified and is available

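### Secondary biomarkers are compared by a t or rank test without baseline adjustment, although each biomarker is measured at baseline; adjustment would be more precise and would always give an effect estimate

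*Protocol*

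**What the plan says.** Protocol section 10 (Statistical Analysis) sets the between-group method for continuous data: Student's t "testing if the data is normally distributed, and non-parametric testing if it is not", with "a two-tailed P <0.05 will be considered to indicate statistical significance". The sentence before it reads "Within-group differences will be shown for each treatment group separately by a mean and a standard deviation (SD"). No covariate is named, and the text does not say whether the between-group test uses those within-group differences or the follow-up values. The section adds "Time to event analysis and logistic regression will be used to analyse outcomes"; neither of these is a model for a continuous biomarker. On baseline it says only "Given randomisation to treatment, baselines will not compared statistically", which concerns testing for imbalance and not adjustment.

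The Study Schedule (part 1, Patient characteristics) lists "Baseline bloods: Biochemical profile (BCP), full blood count (FBC), CRP, PCT, LDH, Troponin, Ferritin, D-Dimer, BNP, lactate", ahead of randomisation. Part 2 repeats these biomarkers daily, for at most ten days and stopping at discharge. Under Outcomes in section 3, biomarker improvement is a secondary outcome. The primary outcome is need for invasive ventilation. Cycle threshold (CT) values enter through time to viral clearance. Sections 2 and 9 give the purpose of the pilot as an effect size for a definitive trial.

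**The concern.** With 20 patients per arm, each biomarker's own baseline is the obvious means of reducing noise, and it is already collected. The stated rule does not use it as a covariate. If follow-up values are tested, baseline plays no part. If changes are tested, baseline is subtracted in full, which adds noise when the correlation is weak.

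The choice of test by normality raises a second matter. Inflammatory and coagulation markers are typically skewed, so the rank branch would often apply. A rank test reported alone gives a P value but no mean difference or ratio with an interval, which is what a pilot of this kind should pass on. What is at stake is precision and a usable estimate for the secondary biomarkers. The validity of the trial is not in question.

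**Working it through.** **Plan's own figure.** Section 9 derives 20 per group from a minimum of 20 degrees of freedom. Per arm, n − 1 = 20 gives 21, close to the stated 20 (which has 19). It gives no power, effect size or SD for any biomarker, so there is no power figure to reproduce.

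**Inputs.** n = 20 per arm and two-sided alpha 0.05 come from the protocol. The baseline-to-follow-up correlation r is assumed, as is equal variance at the two times.

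**Relative variance of the treatment difference** (follow-up-only test = 1):
- change score: 2(1 − r)
- ANCOVA: (1 − r²), times 1 + 1/36 = 1.028 for chance baseline imbalance

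The value per arm is 20 × (better unadjusted variance) / (ANCOVA variance).

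| r | Follow-up | Change | ANCOVA | ANCOVA × 1.028 | Worth per arm, before factor | After factor |
|---|---|---|---|---|---|---|
| 0 | 1 | 2.0 | 1.00 | 1.028 | 20.0 | 19.5 |
| 0.3 | 1 | 1.4 | 0.91 | 0.935 | 20/0.91 = 22.0 | 21.4 |
| 0.5 | 1 | 1.0 | 0.75 | 0.771 | 20/0.75 = 26.7 | 25.9 |
| 0.7 | 1 | 0.6 | 0.51 | 0.524 | 20 × 0.6/0.51 = 23.5 | 22.9 |

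With the factor included, ANCOVA beats the follow-up test when r² > 1/37, that is r above about 0.16. It beats the change score when 2/(1 + r) > 1.028, that is r below about 0.95.

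**Power**, at the effect (0.909 SD) for which the follow-up t test has 80%, with 38 degrees of freedom for t and 37 for ANCOVA (critical values 2.024 and 2.026):

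| r | Follow-up t | Change t | ANCOVA |
|---|---|---|---|
| 0 | 80.0% | 50.9% | 78.9% |
| 0.3 | 80.0% | 65.8% | 82.5% |
| 0.5 | 80.0% | 80.0% | 89.0% |
| 0.7 | 80.0% | 95.1% | 97.2% |

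**The choice by normality.** The protocol names no normality test. The simulation assumed Shapiro-Wilk in each arm at 5%, applied to follow-up values, with 10,000 runs per setting and r = 0.3, 0.5 and 0.7.
- Type I error of the two-stage rule was 5.0% to 5.6%.
- Normal data went to the rank test in 9% to 10% of runs, lognormal data in over 99%.
- For lognormal data at r = 0.5 and an effect of 0.909 SD on the log scale, power was 60% for the t test, 78% for the two-stage rule and 89% for ANCOVA on the log scale.

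**The case against.** The best defence is that an unadjusted t or rank test is valid in a randomised trial, that covariates for secondary outcomes are often left to the statistical analysis plan, and that the gain rests on a correlation the protocol does not give. Validity and the assumed correlation are conceded. The appeal to a later plan is weaker, because section 10 does not leave the test open: it names one.

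Several stronger readings are tempting, and the protocol does not support them.

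- *The plan ignores baseline.* The sentence on within-group differences stands directly before the one on between-group tests, so change scores may be meant. The gains are therefore measured against the better unadjusted option.
- *The rank branch leaves no effect size at all.* Mean and SD of the within-group differences are promised for each arm whichever test is used, and a difference in mean change can be computed from them. This fills the gap only in part: it is not a planned between-group estimate with an interval, and means and SDs describe skewed markers poorly.
- *The normality check inflates false positives, or is too weak at this size to detect skewness.* The simulation shows neither for the distributions tried.
- *Chance imbalance biases the result.* The baseline difference has SD √(2/20) = 0.32 SD, but the unadjusted standard error already allows for it. The loss is in precision.
- *The main result is affected.* The primary outcome is binary, and viral clearance is a time outcome. Although "Baseline SARS-CoV-2 Swab PCR with CT Value (indirect assessment of viral load) through Nasopharyngeal swab" is recorded, section 10 specifies no t test of CT values as such.

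**Conclusion.** The point holds for the secondary biomarker outcomes. Section 10 fixes a less precise method than the collected data allow, and leaves open which quantity is tested. Under assumed correlations of 0.3 to 0.7 and equal variances, baseline adjustment is worth about 21 to 26 patients per arm instead of 20 against the better unadjusted choice, with the largest gain near 0.5. If baseline is unrelated to follow-up, it costs about 1 point of power (80.0% to 78.9%). For skewed markers, the larger practical benefit is a planned between-group estimate with an interval. The change is worth making, but the trial's validity and its primary analysis do not depend on it.

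**What to change.** In section 10, replace the t or non-parametric rule for biomarkers with text such as: each biomarker will be compared between arms by ANCOVA with treatment and the baseline value of the same biomarker as terms, skewed biomarkers on the log scale; the adjusted difference, or ratio of geometric means, will be reported with its 95% confidence interval and the residual SD; a rank test will be a sensitivity analysis.

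Name one early day for this comparison, defined alike in both arms, that nearly all patients reach before discharge. Recording stops at discharge, and section 7 leaves missing values out of the analysis, so a late day would compare only those still in hospital.

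Do not extend this to CT values as a continuous outcome, because a swab that has turned negative has no CT value. Leave CT to the time-to-clearance analysis, where baseline CT may be a covariate.

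The cost is a short rewording and one degree of freedom per model (38 to 37). No new measurements are needed.

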**Outcomes**
Primary outcome is 1) Requirement for invasive ventilation
Secondary outcomes: 1) Time to viral clearance (through the use of CT values) 2) Improvement in biomarkers 3) Radiological Improvement 4) Mortality rate

**Identification of suitable plasma donors among patients recovered from COVID-19**.

Patients who have recovered from COVID-19 and have been discharged from hospital will be approached to see if they will volunteer to be donors

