**2: Daily recording in case report form for 10 days or until discharge**

- blood pressure, temperature, respiratory rate
- Oxygen flow rate and oxygen device for oxygen saturation
- Full blood count(Hb, WBC, Neutrophil count, Neutrophil percent (%),Lymphocyte count, Lymphocyte percent (%),Platelets) , Biochemical profile(Na, K, Urea, Creatinine, LDH), Liver function tests(ALT,AST,ALP,GGT), CRP, PCT, LDH, Troponin, Ferritin, D-Dimer, BNP, lactate
- Date of plasma infusion
- Amount of plasma infusion
- Adverse Event or Adverse Reaction
- Patient’s current medications
- Date of Intubation
- Ventilator Setting if on ventilator

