**9.Sample Size**

There are currently no robust studies in man that would allow for a definitive power calculation and therefore this study can be considered a pilot study with the outcome of providing an effect size that would allow the powering of a definitive study. Power and sample size for pilot studies has been reviewed by Birkett and Day(9). They concluded that a minimum of 20 degrees-of-freedom was required to estimate effect size and variability and hence 20 patients per group have been included in this study; dropouts are unlikely to be an issue in this study.

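### P<0.05 is declared significant for every analysis while the biomarker outcome names no marker or time point, with up to 23 laboratory markers collected daily

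*Protocol*

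**What the plan says.** Protocol section 10 (Statistical Analysis) sets one rule: "For all statistical analyses, a two-tailed P <0.05 will be considered to indicate statistical significance". It does not limit the rule to the primary outcome, label any analysis exploratory, or mention multiplicity.

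The Outcomes list has a single primary endpoint ("Primary outcome is 1) Requirement for invasive ventilation") and four secondary ones: time to viral clearance, followed by "2) Improvement in biomarkers 3) Radiological Improvement 4) Mortality rate". The biomarker item names no marker, time point or direction of improvement.

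The laboratory data come from the Study Schedule, under "Daily recording in case report form for 10 days or until discharge". That list includes "Full blood count(Hb, WBC, Neutrophil count, Neutrophil percent (%),Lymphocyte count, Lymphocyte percent (%),Platelets", then "Biochemical profile(Na, K, Urea, Creatinine, LDH), Liver function tests(ALT,AST,ALP,GGT", and then CRP, PCT, LDH, troponin, ferritin, D-dimer, BNP and lactate.

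Section 9 (Sample Size) gives no power calculation and explains that "this study can be considered a pilot study with the outcome of providing an effect size" for a definitive trial.

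**The concern.** Each sentence is ordinary by itself; the difficulty is the combination. An open-ended outcome can be met by any of many markers, and the protocol has already fixed that each P<0.05 counts as statistically significant. Followed literally, the plan allows one isolated marker out of a long panel to be reported as a significant secondary finding when plasma does nothing.

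Two things are at stake:

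- **Interpretation.** Section 12 foresees urgent reporting of the main findings and several papers, and section 4 (Subject selection) describes the primary aim as showing efficacy. A lone significant marker could be read in that light.
- **The pilot's own purpose.** With 20 per arm, a marker reaches P<0.05 only if its observed difference is large (shown in the working). A marker picked because it is significant would therefore give an inflated effect size for planning the definitive trial.

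A pilot meant to estimate an effect needs estimates with intervals. Section 10 describes within-group means and SDs, tests and a significance threshold, but does not mention a confidence interval for the between-group difference.

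**Working it through.** The plan has no figure to reproduce here: 0.05 is a stipulated threshold and no family-wise error rate is stated.

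**Inputs**

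- Per-test level: 0.05 two-sided, that is 0.025 in the direction favouring plasma (section 10).
- Markers in the daily schedule: 7 (full blood count) + 5 (biochemical profile) + 4 (liver function) + 8 (the closing group) = 24 entries. LDH appears twice, so 23 are distinct.
- Sample: 20 per arm, so a t test has 20 + 20 − 2 = 38 degrees of freedom.
- Correlation between markers: not given in the protocol. Common values of 0.3, 0.5 and 0.7 are assumed to show a range.

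**All 23 markers, one comparison each, no true effect**

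Under independence, P(at least one) = 1 − (1 − α)^k.

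- Either direction: 1 − 0.95^23 = 0.693. Expected false positives: 23 × 0.05 = 1.15.
- Favouring plasma: 1 − 0.975^23 = 0.441. Expected: 23 × 0.025 = 0.575.

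With equal correlation the probabilities come from simulating 20 versus 20 patients under the null with t tests (4,000 trials per setting, standard error below 1 percentage point):

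| Assumed correlation | Either direction | Favouring plasma |
| --- | --- | --- |
| 0 (formula) | 69% | 44% |
| 0.3 | 58% | 31% |
| 0.5 | 45% | 22% |
| 0.7 | 30% | 15% |

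**A narrower reading: only the 8 markers in the closing group (CRP to lactate)**

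Either direction under independence: 1 − 0.95^8 = 0.337, or 34%. At correlations of 0.3 to 0.7 it is about 30% to 19%.

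**Comparison with the nominal level**

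The lowest favourable-direction figure in the table is 15%, and 15 / 2.5 = 6 times the nominal 2.5%. The lowest either-direction figure for 8 markers is 19%, and 19 / 5 = 3.8 times the nominal 5%.

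**Size of effect needed for P<0.05**

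The critical t on 38 degrees of freedom is 2.024. The smallest observed standardised difference reaching significance is 2.024 × √(2/20) = 0.64. Any marker selected for significance by this test will show at least that difference, even if the true difference is zero.

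**The case against.** The strongest reply is that this belongs to the SAP. The trial has one primary outcome, a nominal 0.05 threshold is conventional, and the choice of markers, time point and multiplicity handling is commonly settled there. That stands for the choice of markers: leaving them unnamed in the protocol is not itself the fault. It does not rescue the significance rule, which is an affirmative statement about all analyses. A SAP that treated secondary outcomes as exploratory would have to depart from it.

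Several stronger readings are tempting, and the protocol does not support them:

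- **That all 23 markers form the outcome.** The schedule is a data-collection list that also holds vital signs, medications and adverse events. Some items, such as sodium and potassium, have no stated direction of improvement. The supportable wording is up to 23.
- **That a chance improvement is likely.** The 69% counts either direction and assumes independence. In plasma's favour the figure is at most 44% for one test per marker, and lower with correlation. Independence is implausible here, since neutrophil count and percent, for example, are linked by construction.
- **That markers will be tested every day.** Daily recording is stated; daily testing is not.
- **That the small sample causes the false positives.** The rate depends on the level, the number of tests and their correlation. Sample size affects only how large a significant difference must look.

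It is also fair to object that 23 unadjusted 95% intervals exclude the null as often as 23 tests at 0.05. Replacing P values by intervals changes the claim, not the arithmetic, so the new wording must say what such an interval means.

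**Conclusion.** The point holds in a limited form. Section 10 fixes a significance rule that, applied as written to an open-ended biomarker outcome, leaves a false-positive rate well above nominal in every scenario examined. For one comparison of each of 23 markers, the rate is 30% to 69% in either direction and 15% to 44% in favour of plasma. With 8 markers it is 19% to 34% in either direction. These figures rest on no true effect, one comparison per marker, and assumed common correlations from 0 to 0.7; the number of markers that will count as biomarkers is not known from the protocol.

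The primary outcome's error rate is untouched. The consequence is confined to what may be claimed from secondary markers and to the effect sizes carried forward. It is worth correcting because the rule sits badly with the pilot's stated purpose and the correction is nearly free.

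**What to change.** Replace the significance sentence in section 10 with wording to this effect: the two-sided 0.05 level applies to the primary outcome only; all secondary outcomes, including each biomarker, are exploratory and are reported as between-arm estimates with 95% confidence intervals, without any claim of statistical significance; an interval that excludes the null is not confirmatory evidence.

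No alpha adjustment, extra patients or additional data are needed. The cost is one sentence of wording, and the downside is that no significance claim can be made for a secondary marker.

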**2.Objectives**

**Primary objective**

The objective of this pilot study is to compare plasma therapy using convalescent plasma with antibody against SARS-CoV-2 to usual supportive therapy in COVID-19 patients with pneumonia and hypoxia, and to determine if the clinical course is improved. The difference between groups will allow an effect size to be determined for a definitive clinical trial

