**5. Randomisation**

The study will randomise the patients to one of 2 groups randomised by computer. The number of patients in each group will be the same and they will have an equal chance of being in either arm of the study. Randomisation code will be provided by RCSI Bahrain to be administered in the local environment.

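### Neither the randomisation nor the stated models use baseline oxygenation, which is collected; pre-specifying one covariate would make the pilot's effect size more precise at little cost

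*Protocol*

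**What the plan says.** The pilot's purpose is estimation. Under Primary objective: "The difference between groups will allow an effect size to be determined for a definitive clinical trial". Section 9 repeats this as the reason for having no power calculation.

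The primary endpoint is binary: "Primary outcome is 1) Requirement for invasive ventilation".

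On allocation, section 5 says: "The study will randomise the patients to one of 2 groups randomised by computer". The groups are to be of equal size, and no stratification factor or minimisation is named. Section 4 (Subject selection) declines stratification by gender and does not mention severity.

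The Study Schedule (1: Patient characteristics) lists "COVID-19 oxygen therapy being given, oxygen saturation on room air, oxygen flow", together with a room-air blood gas and a baseline PaO2. Randomisation is the last item of that list.

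On analysis, section 10 says "Time to event analysis and logistic regression will be used to analyse outcomes", with no covariate named. It also says "Between-group comparisons will be performed using Student’s t testing if the data is normally distributed, and non-parametric testing if it is not", which depends on normality and so does not describe a yes/no endpoint. It rules out significance tests at baseline ("Given randomisation to treatment, baselines will not compared statistically"), which is sound and is a separate matter from covariate adjustment.

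**The concern.** Patients enter hypoxic and on oxygen but not yet needing ventilatory support, and the primary endpoint is progression to invasive ventilation. How hypoxic a patient is at entry is a natural candidate for a prognostic factor. With 20 per arm and no severity factor in the randomisation, the arms can differ at entry by chance, and the single estimate carried forward to size the definitive trial will include that difference. The protocol collects the measurements that could remove much of this noise, but as written neither the design nor the analysis uses them. What is at stake is the precision of the pilot's one main output, not its validity.

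**Working it through.** **The plan's own figure.** Section 9 takes 20 per group from a rule of 20 degrees of freedom and gives no event rate, effect or power, so there is no power figure to reproduce. Read per arm (n − 1 = 20), the rule gives 21. Read as pooled (2n − 2 = 20), it gives 11, and 20 per arm gives 38 pooled degrees of freedom. The point below does not depend on which reading was meant.

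**Inputs.** From the protocol: 20 per arm, equal allocation, binary endpoint. Assumed, because the protocol gives none: ventilation rates, treatment effect and the prognostic strength of baseline oxygenation.

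**Step 1: how often the arms differ in severity.** For a baseline measure in SD units, the standard error of the difference in arm means is √(1/20 + 1/20) = 0.316.
- Above 0.25 SD: 2 × (1 − Φ(0.25/0.316)) = 0.43
- Above 0.5 SD: 2 × (1 − Φ(1.58)) = 0.114
- Above 0.75 SD: 0.018

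**Step 2: what an imbalance does to the risk difference.** Simulation: 20 per arm, 20,000 trials per case, treatment log odds ratio −0.8, one normally distributed severity measure, crude versus linearly adjusted risk difference. The shifts are for trials in which the intervention arm was sicker by about 0.5 SD.

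| Control rate | Severity log OR per SD | Crude shift (points) | Adjusted shift (points) | Variance ratio, adjusted/crude |
|---|---|---|---|---|
| 20% | 0.5 | 3.1 | 0.1 | 0.991 |
| 20% | 1.0 | 5.0 | −0.5 | 0.931 |
| 20% | 1.5 | 7.6 | 0.2 | 0.837 |
| 30% | 0.5 | 3.6 | −0.4 | 0.989 |
| 30% | 1.0 | 7.5 | 0.1 | 0.892 |
| 30% | 1.5 | 9.5 | −0.7 | 0.801 |
| 40% | 0.5 | 4.6 | −0.3 | 0.982 |
| 40% | 1.0 | 8.8 | −0.2 | 0.880 |
| 40% | 1.5 | 11.6 | −0.1 | 0.773 |

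Averaged over all randomisations, both estimates were within about 0.2 points of the truth. Adjustment cut the variance by 1–2% (weak covariate), 7–12% (moderate) and 16–23% (strong).

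**Step 3: the proposed estimator.** A penalised (Firth) logistic model with arm and one covariate, reported as a standardised risk difference, was simulated at 20 per arm under assumed rates.
- With a useless covariate, its root mean squared error was no worse than that of the crude difference (about 0.13 against 0.13–0.14).
- At correlations of 0.3 to 0.5 with the outcome, it was 10–20% lower.
- Coverage of the 95% interval was 95–97%, against 92–95% for the crude difference. Bias was at most 1.5 points.

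Not all of this gain comes from the covariate. In a two-arm Firth model each arm's rate becomes (x + 0.5)/21, which multiplies the risk difference by 20/21 = 0.952. Combined with the variance ratios in step 2, √0.892 × 0.952 = 0.90 and √0.773 × 0.952 = 0.84, that is, 10% and 16% lower. About 5 percentage points of the reduction are therefore shrinkage. The cost of that shrinkage is bias towards zero of 1/21 of the true difference: 15/21 = 0.7 points for a 15-point difference and 30/21 = 1.4 points for a 30-point one.

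**Step 4: scale of the remaining error.** At an assumed 30% versus 15% ventilated, the standard error is √(0.30 × 0.70/20 + 0.15 × 0.85/20) = 0.130. The 95% half-width is 1.96 × 0.130 = 25.5 points, and 20 × 0.30 + 20 × 0.15 = 9 events are expected.

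**The case against.** A reader might infer that the primary comparison is planned as unadjusted. The protocol does not say so. Logistic and time-to-event models can both carry covariates, and the list is commonly left to a statistical analysis plan, which is not at hand. That stands: the silence is not an error, and the point is an improvement only.

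A reader might also infer that chance imbalance passes straight into the effect size and biases it. That is too strong. Randomisation keeps the crude difference unbiased, and its confidence interval already allows for imbalance. The small number of events is the larger source of error, as step 4 shows.

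The gain is uncertain. The protocol supports no particular correlation, and the entry criteria narrow the range of oxygenation, which tends to weaken it. In a simulation of power at 30% versus 10% ventilated, adjustment moved power from 34% to 34% at a correlation of 0.26. At 50% versus 20% it moved from 47% to 59% at a correlation of 0.42. Power is in any case a secondary yardstick for a study that claims none.

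Two practical objections also stand. Section 7 leaves missing values out of the analysis, so a patient without the baseline value would drop out of an adjusted model; the fix has to prevent that. And choosing saturation over PaO2 or oxygen flow is a matter of judgement; what matters is that one is named in advance.

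None of this removes the case for adjusting. The measure is already planned, and the simulated estimator lost nothing when the covariate was useless.

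**Conclusion.** The point holds as a cheap gain in precision of uncertain size, not as a fault in the protocol. Neither section 5 nor section 10 uses baseline oxygenation, although the schedule collects it before randomisation. The 11% chance of an imbalance above 0.5 SD needs only the sample size and a normal approximation. The benefit rests on assumed event rates and correlations: little or nothing from the covariate if it is weakly prognostic, and roughly 10–20% lower root mean squared error at correlations of 0.3 to 0.5, part of it from the penalty. Naming the covariate now also matters because the trial is open label and section 11 plans a review at 20 recruited subjects, so a covariate chosen late could be chosen with outcomes in view.

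**What to change.** In section 10, state in advance that:
- the primary logistic model is penalised, because events will be few, and contains treatment arm and one continuous baseline oxygenation measure, for example room-air saturation;
- the result is reported as a standardised risk difference with a 95% confidence interval, beside the crude proportions, so that it can be used directly to size the definitive trial (an adjusted odds ratio is conditional and differs from the marginal one even with perfect balance);
- the time-to-event model uses the same covariate;
- a missing baseline value is imputed, for example by the mean over both arms, so that the missing-data rule in section 7 does not remove a randomised patient from an intention-to-treat analysis.

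The cost is a few lines of analysis text, with no new data, visits or patients. The statistical price is one extra parameter with few events, hence the limit to one covariate, and shrinkage of the risk difference by about 1 point from the penalty.
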